### Study design

An online experiment was conducted through a 2 (appeal: individualistic or collectivistic) x 2 (tone: humor or non-humor) x 2 (protagonist gender: male or female) between-subjects design. Participants were recruited through a link posted on the Swasthya Plus Network (SPN) Odia website, and was shared by SPN on their public Odia WhatsApp channels. In order to be eligible for the study, participants needed to be between the ages of 18–35, and speak Odia. We did not check for language ability as the recruitment pages, channel, survey, and videos were all in Odia. Odia-speaking participants (N = 2,700) between the ages of 18–35 years were randomly assigned to watch one of the eight study videos, providing their vaccination attitudes, beliefs, and intentions both before and after viewing the videos. We tested for main effects of appeal, tone, and protagonist gender (as well as the underlying two-way and three-way interactions). During script development, we also sought the feedback from a community advisory board for cultural appropriateness. Videos were shot in December 2021 and the experiment itself was launched in January 2022.

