**b.   Pre-exposure questions**

We started the survey by asking the respondents about their age, gender and their vaccination status. Participants who indicated that they had not received a COVID-19 vaccine were asked what their primary reason was for refraining from getting the particular vaccine. In an effort to understand attitudes and beliefs about COVID-19 vaccines (including vaccine hesitation towards COVID-19), participants were asked to rate their agreement on a series of statements adapted from Quinn
*et al*. (2019) on a five-point Likert scale from “strongly disagree” to “strongly agree”
^
10
^. Additionally, we asked how often and how likely specific COVID-19 thoughts had entered their minds in the last three months including the likelihood of contracting COVID-19 and the frequency that they thought about COVID-19 vaccinations. Finally, we included 13 questions about collectivism and individualism from Singelis
*et al*.’s 1995 vertical and horizontal collectivism and individualism scale
^
42
^. The three statements of each type of collectivism/individualism with the highest factor loadings along with one very culturally appropriate statement about family was included in the questionnaire.

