## Measurement

### Statistical analysis and power calculation

**Online experiment component:** We assumed that, prior to exposure, 30% of the population would be vaccine-hesitant and that exposure would affect the attitudes of 10% of the viewers. To achieve power of 80%, with an alpha of 5%, the required sample size would be 294 per group, which we rounded up to 300. To be able to conduct sub-analyses along caste (three subgroups) and three age groups (i.e., nine groups in total), the overall required sample size was calculated to be 2,700. 

**Data analysis**. Data analysis will be done in two phases. First, we will conduct manipulation checks for the three variables that were manipulated. We manipulated the scripts to have either an individualistic or a collectivistic appeal. Responses to questions that asked about the extent to which the videos had an individualistic appeal (coded as 1) or a collectivistic appeal (coded as 5) will be subjected to a t-test in which the assignment to condition (individualistic or collectivistic) will be the independent variable. Similarly, the extent to which the videos were perceived to be humorous will also undergo a t-test. Finally, we will ask participants to recall whether the main protagonist was a male or female. This will be compared against the assignment variable (whether assigned to the male or female protagonist) through a chi-square test. If the results of the two t-tests and the chi-square test are significant, we will deem the manipulations to have been successful. Second, we will run an analysis of covariance (ANCOVA) model in which assignment to experimental conditions will be the three independent variables (individualistic or collectivistic appeal; humor or serious tone; and protagonist gender) and attitudes toward vaccines will be the dependent variable. In this model we will control for demographic indicators. We will also test for three two-way and one three-way interactions among the independent variables.

**Qualitative component:** From the survey respondents (
*n*=2,700), we will identify the 10% (

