*n*=270) with greatest vaccine hesitancy, as determined through their pre-exposure scores on the vaccine confidence index. This subsample will be invited to participate in focus groups. From this pool, we will purposively select participants to fill up to 12 focus groups, each with 8 participants. To ensure we hear diverse viewpoints from different segments of the population, groups will be stratified by both age (18–22, 23–30, 31–45) and gender (male, female). Following this design, we expect a maximum of 100 participants (
Table 2).

**Table 2. T2:** Expected numbers and description of focus group (FG) participants.

	Male	Female	Total
Age 1: 18–22 years	2 FGs ( *n*=16)	2 FGs ( *n*=16)	4 FGs ( *n*=32)
Age 2: 23–30 years	2 FGs ( *n*=16)	2 FGs ( *n*=16)	4 FGs ( *n*=32)
Age 3: 31–45 years	2 FGs ( *n*=16)	2 FGs ( *n*=16)	4 FGs ( *n*=32)
Total	6 FGs ( *n* =48)	6 FGs ( *n* =48)	12 FGs ( *n*= 96)

Additionally, time and resources have been allocated to conduct semi-structured online interviews with up to 20 additional people to delve deeper on any emergent topics that may arise over the course of the study. This would lead to a maximum of 120 participants in the qualitative portion of the study.

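### The outcome ANCOVA names only demographic covariates and omits the pre-exposure attitude score, an avoidable loss of precision

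*Protocol article*

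**What the plan says.** All references are to the Protocol article; no separate SAP is shown.

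- **Outcome model** (Statistical analysis and power calculation, Data analysis). It is an ANCOVA in which "assignment to experimental conditions will be the three independent variables" and "attitudes toward vaccines will be the dependent variable". The text does not say whether this is the post-exposure score or a change from baseline.
- **Covariates** (same paragraph). "In this model we will control for demographic indicators". Nothing else is named.
- **Interactions** (same paragraph). "We will also test for three two-way and one three-way interactions among the independent variables".
- **Pre and post measurement** (Study design). Randomised participants are described as "providing their vaccination attitudes, beliefs, and intentions both before and after viewing the videos".
- **Baseline items** (b. Pre-exposure questions). Before the video, "participants were asked to rate their agreement on a series of statements", on a five-point Likert scale.
- **Baseline score in use elsewhere** (Statistical analysis and power calculation, Qualitative component). The most hesitant 10% are picked for focus groups "as determined through their pre-exposure scores on the vaccine confidence index".

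**The concern.** The trial collects a baseline measure of the construct it wants to change, and scores it for another purpose. The one sentence that chooses covariates for the outcome model leaves it out. A person's attitude some minutes earlier in the same survey is likely to predict the later attitude better than age, gender or caste does. Without it, stable differences between people stay in the error term.

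This matters because all eight arms are active videos, made to be identical apart from the three manipulated features, so contrasts between them are likely to be small. The primary research question also asks how the features act jointly, which puts weight on the interactions. A two-way difference in differences has twice the standard error of a main effect in any balanced 2 × 2 × 2 design, so there is little precision to spare. The article reports 2,349 responses against a planned 2,700, which makes precision available from existing data worth more.

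**Working it through.** **1. The plan's own figure.** The article assumes that "prior to exposure, 30% of the population would be vaccine-hesitant", that 10% of viewers are affected, 80% power and 5% alpha, and states 294 per group. Reading this as 30% versus 20%, two-sided, with pooled variance under the null:

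n = [1.960 × √(2 × 0.25 × 0.75) + 0.842 × √(0.3 × 0.7 + 0.2 × 0.8)]² / 0.10² = (1.200 + 0.512)² / 0.01 ≈ 293.2, so 294.

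The figure reproduces. It is a two-proportion calculation and does not depend on the ANCOVA covariates, so it does not settle the present point.

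**2. Inputs for the precision check.**
- N = 2,349 responses (Online experiment), taken as all analysable and evenly spread over the arms; planned N = 2,700.
- Each factor has two levels, so about N/2 per level.
- r = correlation of pre- and post-exposure scores after demographics. It is not in the article and is assumed to be 0.5 to 0.8.
- Effects are in units of the residual SD of the post-exposure score after demographics, so the r = 0 row below is the demographics-only model.

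**3. Post-exposure score as the dependent variable.** Adding the baseline score multiplies residual variance by (1 − r²).

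- SE of a main effect = 2√(1 − r²)/√N. At N = 2,349 and r = 0 this is 2/48.47 = 0.0413.
- Detectable effect with 80% power = (1.960 + 0.842) × SE. At r = 0 this is 2.802 × 0.0413 = 0.116.
- Two-way interaction (difference in differences): SE = 4√(1 − r²)/√N, twice the main-effect value.

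| r | Residual variance left | Detectable main effect, N = 2,349 | Detectable two-way interaction, N = 2,349 | Power for a 0.10 SD main effect, N = 2,349 | Detectable main effect, N = 2,700 |
|---|---|---|---|---|---|
| 0 | 100% | 0.116 SD | 0.231 SD | 68% | 0.108 SD |
| 0.5 | 75% | 0.100 SD | 0.200 SD | 80% | 0.093 SD |
| 0.7 | 51% | 0.083 SD | 0.165 SD | 92% | 0.077 SD |
| 0.8 | 36% | 0.069 SD | 0.139 SD | 98% | 0.065 SD |

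The 0.10 SD effect is illustrative. The equivalent gain in sample size is 1/(1 − r²): 1.33, 1.96 and 2.78 times for r = 0.5, 0.7 and 0.8.

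**4. Change score as the dependent variable.** With equal pre and post SDs, an unadjusted change score has variance 2(1 − r), against 1 − r² for baseline-adjusted ANCOVA. The ratio is (1 + r)/2.

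| r | Change score, 2(1 − r) | ANCOVA, 1 − r² | Saving from adjustment |
|---|---|---|---|
| 0.5 | 1.00 | 0.75 | 25% |
| 0.7 | 0.60 | 0.51 | 15% |
| 0.8 | 0.40 | 0.36 | 10% |

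Adjustment helps under either reading, but by less at high r if a change score was meant.

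**5. Order of the questions.** Age, gender and vaccination status are asked before the video (b. Pre-exposure questions). The general demographics come last, after social media use (d. Post-exposure questions). A complete-case model with those late items loses anyone who answers the attitude items and then stops. The baseline score and the early items do not carry that risk.

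**The case against.** **The article is condensed, and a fuller plan might include the baseline score.** That is possible. But the article is not silent on covariates: it makes a choice and states it, and the choice omits the baseline score. The point is about what is written.

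**The dependent variable may be a change score.** The text permits this reading, and a change score would already use the baseline. This stands, and it is why step 4 gives the smaller gain. It also means the dependent variable itself needs to be stated.

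**Repetition of the same items is not shown.** The section on post-exposure questions lists reactions, manipulation checks, recall, credibility, social media use and demographics, but no repeated attitude items. Study design does say in general terms that attitudes, beliefs and intentions were given both times. The list may simply be abbreviated, but item-for-item repetition and complete response are not established.

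**Stronger readings that the article does not support.**
- A reader might infer that the plan gives up most of the available precision. Residual variance is more than halved only if r exceeds about 0.71, and the article gives no r.
- A reader might infer bias from chance imbalance between arms. Assignment is random, so the demographics-only contrast is unbiased and its standard error already allows for chance imbalance.
- A reader might infer that the omission harms interactions more than main effects. The factor √(1 − r²) is the same for both; interactions only start from larger standard errors.
- A reader might infer that everyone who quits after the video is lost because of the late demographic questions. Someone who quits before the post-exposure attitude items has no outcome in any model.

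**Conclusion.** The point holds as a loss of efficiency. The outcome model names only demographic covariates, and no section gives the pre-exposure attitude score a role in it, although that score is collected and used to select focus-group participants.

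If the post-exposure score is analysed, the residual variance given up is r², or 25% to 64% for r between 0.5 and 0.8. That is the difference between a detectable main effect of 0.116 SD and one of 0.100 to 0.069 SD at N = 2,349. If a change score is analysed, the loss is 25% down to 10% over the same range. These sizes rest on an assumed correlation, on all 2,349 responses being usable pre/post pairs in near-equal arms and, for the change score, on equal SDs. The direction of the gain is firm; its size is not known from the article. The change should be made, but the analysis as written is not invalid.

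**What to change.** - State that the dependent variable is the post-exposure attitude score.
- Add the pre-exposure score of the same scale as a prespecified covariate alongside the demographics, and confirm that the same items are asked both times.
- Do the same in any model for beliefs and intentions.
- Where possible, take covariates from the pre-exposure block (baseline score, age, gender, vaccination status), so that people who answer the attitude items but stop before the final demographic questions stay in the model.
- Record the change before outcomes are compared between arms. If that comparison has already been made, date the change and report the demographics-only model beside it.

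The cost is a sentence or two in the analysis section and one degree of freedom per model. On the Study design account of pre and post measurement, no new data are needed.

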## Results

Ultimately, findings from this work will provide guidance to health communication professionals on how to frame their vaccination messages regarding whether appealing to the collective good or the individual benefit. In addition, when and how to use humor, and how male and female protagonists garner different reactions among different audiences will be determined. We also want to understand how these factors may work synergistically. The overall goal is to explore which combinations of messaging features have the greatest impact to reduce vaccine hesitancy and boost confidence in vaccination. Through the qualitative analysis, we have the opportunity to gain a deeper understanding of these specific message features and their relevance to the vaccine-hesitant in Odisha. Through the social network analysis, we will explore the connections between users and gain insight into information-seeking behaviors around vaccines. While this project is narrowly focused on COVID-19 vaccine, we anticipate that valuable insights gleamed from this work will have important implications for messages on vaccination for other diseases and elucidate how to craft and disseminate messages through brief videos on the Internet.

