### Video scriptwriting

Many vaccination messages put out by the Indian government use a public service announcement structure in which people are urged to get vaccinated in order to ward off the disease and derive positive benefits, with a primary messaging strategy built around providing accurate vaccine information
^
68
^. In this project, we adopted a different approach so that our videos would stand out from the din of government-produced announcements. Borrowing ideas from entertainment education
^
69
^, we chose to depict a common social event (e.g., a child’s birthday) in which vaccination issues would be brought up in an incidental manner, not as the primary thrust of the communication.

The creative team identified various real-world mixed-gender, mixed-age settings that would fit these criteria. Finally, a private social occasion of the birthday of a young family member was selected to be the setting for the video. Within this broad setting, we manipulated appeal, approach, and gender to create eight videos that were identical, except in the variables that were being manipulated. The creative team in Odisha developed the scripts in Odia, the language the videos were filmed and produced in. English translations were used for discussions and feedback with the larger group, which consisted of health communication experts and a former Hollywood scriptwriter with expertise in storytelling. This approach to develop in Odia first, instead of transforming an English script to the language, improved the likelihood that the videos would be culturally relevant.

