### Video pre-production

**
*Camera & production crew*
**

A professional production team was engaged, consisting of a national-award winning filmmaker, an assistant director, a director of photography, and other crew members. Production logistics were designed to ensure that all the shots would look similar, which meant that the set décor, props, clothing and look etc. would be similar across the multiple days of shooting. A Black Magic Ursa MiniPro 4.6k camera with CP3 lenses was used to film the videos. The Final Cut Pro X was used for editing and the Davinci Resolve 17 was used for color grading on a MacOS.

**
*Casting*
**

For the role of the protagonist, versatile actors able to act in non-humorous as well as humorous roles were selected through auditions. Other actors were recruited based on earlier roles they had portrayed in various media productions. The cast members also understood the scientific aspects of the project, such as the need for reducing improvising in acting and to remain aligned with the script.

**
*Location selection*
**

Various locations were scouted, before deciding on the final location, which was a house in a village near Puri, Odisha, which reflected a rural/ semi-urban setting. The location fit well in the story and was also visually appealing.

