### Post-production editing

 The editing process began with the selection and cataloging of shots as per the various scripts. The first video was created with all the shots and their sequences in the video being documented. The remaining videos were created by using the first video as a template and changing the specific shots as necessary. Put another way, we did not shoot each video from beginning to end before shooting the subsequent video. Rather, we kept the camera focused in a particular way and then shot all eight scenes pertaining to that camera angle before moving on to the next scene. A sample of the shot list for the template video is shown in
Table 1 which was used as a guide to ensure consistency across the eight videos. Each video was subsequently reviewed by a member of the creative team well versed with the research needs and aims, to ensure similarity as well as accuracy in the variations. This post-production editing can be a complex process due to a high volume of seemingly similar but different shots, especially if the creative team members are not familiar with this approach of making videos.

**Table 1. T1:** Description of shot list sample from the template video.

Video	Start	Stop	Camera	Scene
**Template**	0.00	0.03	Close up	Cake being cut
	0.04	0.07	Close up	Helmet on Table
	0.08	0.11	Wide	Munna (the male protagonist) being greeted
	0.12	0.15	Two shots	Handing cake

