**d.   Post-exposure questions**

After being randomized to view one of the videos, participants were asked about their reactions, including the extent to which they found the video to be important, or relevant or caused them to reflect about the COVID-19 vaccine. Participants were also asked about the tone of the video as a manipulation check to gauge whether the humorous videos were perceived as humorous, whether the collectivistically oriented videos were perceived as such, and the extent to which viewers correctly remembered the protagonist gender. We also asked questions about the characters in the video to assess recollection. This included items on source credibility adapted from McCroskey & Teven (1999)
^
76
^. Lastly, we collected information about participants’ social media use, followed by their general demographic information.

**
*Qualitative component*
**

Qualitative research will focus on eliciting the reactions from vaccine-hesitant individuals, identified through the online survey. Our local partners at D-COR will conduct 12 online focus groups, to discuss participant's beliefs and reactions to the videos. Focus groups will be stratified by both age and gender. Of the pool of participants who agree to participate in the qualitative work, eligibility will be decided based on their age and gender (to get a sound distribution of age and gender groups). Focus groups will run for 90 minutes and be conducted in Odia. In the first half of the focus group, moderators will guide discussion around beliefs and attitudes around vaccines – both COVID-19 and vaccines in general – and invite participants to share their concerns. In the second half of the focus groups, participants will be invited to share their reactions to the videos.

 We also plan to conduct up to 20 semi-structured interviews with individuals who may prefer the one-on-one format. This also provides more flexibility for the research team to delve deeper into any emergent themes that may arise during focus groups.

**
*Social media analysis component.*
**

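### The protagonist-gender terms compare the filmed videos with the performers cast; they cannot separate protagonist gender from performer, so the conclusion promised in Results is too broad

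*Protocol article*

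**What the plan says.** Protagonist gender is one of the three factors in the primary research question. Under Video scriptwriting, the article states that "we manipulated appeal, approach, and gender to create eight videos that were identical, except in the variables that were being manipulated". The list under Video randomization shows one video per cell, so four have a male and four a female protagonist.

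On casting, Video pre-production says: "For the role of the protagonist, versatile actors able to act in non-humorous as well as humorous roles were selected through auditions". It does not say how many protagonist actors were used. The sample shot list in Post-production editing (Table 1) has the entry "Munna (the male protagonist) being greeted", which describes the template video only.

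Under Statistical analysis and power calculation, the ANCOVA is specified so that "assignment to experimental conditions will be the three independent variables", with demographic covariates, three two-way interactions and one three-way interaction. The check on the gender manipulation is that "we will ask participants to recall whether the main protagonist was a male or female".

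The Results section then promises, without a stated limit, that "how male and female protagonists garner different reactions among different audiences will be determined", in a paragraph that offers guidance to health communication professionals.

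**The concern.** In live-action film, changing the protagonist's gender changes the performer, and with that the look, likeability, delivery and comic skill. Randomisation balances viewers across videos. It does nothing to balance performers across genders. With one film per cell and no replicate performers, a difference between the male and female films may come from gender, from the performers, or from both, and no term added to the model could divide it.

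The interactions share the problem. A tone-by-gender interaction could arise because one performer is funnier than another. The planned recall check would succeed however much the performers differed in appeal, because it asks only whether the viewer remembers the protagonist's gender.

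At stake is advice on whether to cast men or women in vaccine messages, when the evidence may describe only the people cast in these films.

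**Working it through.** **The plan's own figure.** The article computes nothing for the gender contrast. Its one computed figure, 294 per group, reproduces when 30% is compared with 20% (two-sided 5%, 80% power, pooled variance): [1.960 x sqrt(2 x 0.25 x 0.75) + 0.842 x sqrt(0.21 + 0.16)]^2 / 0.10^2 = 293.2, rounded up to 294. That figure is not in dispute here.

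**What the design identifies.**
- Films per cell: one (Video scriptwriting; Video randomization).
- Performers per gender: not stated. Casting each protagonist actor for both tones suggests one per gender. Eight films allow at most four.
- Held similar across films: dialogue length, set, props, clothing, shots and editing (Pilot-testing; Video pre-production; Video production approach; Post-production editing). Cast members understood the need to limit improvisation.
- Replicated or matched within gender: nothing described for performers. Pretesting used audio recordings with a single female narrator, so it did not compare the performers.

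The gender contrast is therefore the sum of any gender effect and any performer difference. The data cannot separate the two.

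**Illustration of size.** Assumptions, none taken from the article except the response count: 2,349 responses (Online experiment) split evenly by protagonist gender; no true gender effect; covariates ignored; performers of the same gender differ in the mean attitude they produce with SD t, in outcome SD units; k performers per gender with equal numbers of viewers.

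SE of the contrast = 2/sqrt(2349) = 0.0413.

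Total SD = sqrt(0.0413^2 + 2t^2/k).

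Chance of a significant contrast = 2 x [1 - Phi(1.96 x 0.0413 / total SD)].

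With k = 1:
- t = 0.025: total SD 0.0543, chance 14%
- t = 0.05: total SD 0.0819, chance 32%
- t = 0.10: total SD 0.1473, chance 58%

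With k = 4, the most that eight films allow, t = 0.05 gives 14% and t = 0.10 gives 32%. The problem shrinks but remains, and performer would then be confounded with appeal and tone as well.

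More viewers do not help. At the planned 2,700 the SE is 2/sqrt(2700) = 0.0385, and with k = 1 the chances for t = 0.05 and 0.10 rise to 35% and 61%.

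**What these percentages mean.** They are error rates only for the general claim that protagonist gender matters. For the question whether viewers reacted differently to these films, the relevant variance is that of the randomised viewers, and the test keeps its 5% level.

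**The case against.** Several points on the other side are sound.

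- A reader might infer that exactly two performers were used. The article never says so. The named male protagonist is a character in a sample shot list for one video. One performer per gender is likely but remains an inference.
- A reader might infer that the statement that the videos are otherwise identical is false. It is not an error: gender is listed among the manipulated variables, and a different performer follows from that.
- A reader might infer that the ANCOVA is invalid or has an inflated type I error. It is a valid comparison of the filmed videos. Only the step from these films to protagonists in general is unsupported.
- The percentages rest wholly on assumed between-performer SDs.
- Gender is not alone. Tone and appeal also rest on particular scripts in one setting, which is a usual limit of experiments with one film per condition. If the same performers appear across tone and appeal, those two factors are at least balanced over performers.

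It can also be said that the Results text is a forward-looking aim in a condensed article, and that caveats usually appear in the final report. The background also allows that context matters and that gender may not be relevant. This carries less weight. The finding rests on an affirmative, unlimited promise in the text, not on a detail left to a fuller document.

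**Conclusion.** The concern holds as a limit on interpretation. The design supports a randomised comparison of the filmed male-protagonist and female-protagonist videos. It does not support determining how male and female protagonists differ in general, because gender and performer are confounded. That conclusion needs no assumption about how many performers there were. The 14% to 58% range does: it assumes one performer per gender, an even split of 2,349 responses, no true gender effect and between-performer SDs of 0.025 to 0.10. If the performers happened to be equally persuasive, there would be no inflation, but this design cannot show whether they were.

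A tempting further step is to use the post-exposure ratings as a diagnostic ("This included items on source credibility adapted from" a published scale). The article does not support that. Its own section on protagonist gender says that a source's gender can affect credibility, so a difference in ratings would be expected from a true gender effect as much as from a performer difference.

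**What to change.** In Statistical analysis and power calculation, and again in Results, state that:

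1. the protagonist-gender main effect and interactions estimate differences between the filmed male-protagonist and female-protagonist videos, with the performers cast;
2. performer and gender are confounded in these films;
3. these terms will not be presented as a general effect of protagonist gender;
4. tone and appeal effects are likewise specific to the scripts used.

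Replace the unlimited promise in Results with this wording, and state the number of protagonist actors. Do not use the source-credibility items to separate performer from gender, and do not adjust the main model for them, since they are measured after exposure.

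The videos are already filmed, so replicating performers is no longer a cheap option. The change costs a few sentences and should be made before the experiment's results are interpreted. Its downside is a narrower claim for one of the three factors.
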